### 2.4. Participant Recruitment

Although baseline assessments and the intervention have not yet commenced, participant recruitment and randomization have already been completed. A convenience sampling method was employed to recruit middle-aged and older adults through direct communication and email outreach within the senior university program at the University of Almeria. All potential participants were contacted individually.

To be included in the study, participants were expected to meet the following criteria: (a) aged 55 or over; (b) being physically independent; (c) being enrolled in the university for seniors’ program; and (d) passing a medical examination prior to participation, including an electrocardiogram (EKG) under stress conditions. The exclusion criteria were: (a) engaging in moderate or vigorous cardiovascular exercise systematically (≥150 min per week); (b) performing strength training systematically in the last 2 months; (c) having a body mass index (BMI) greater than 35 kg/m^2^; (d) diagnosed with ischemic heart disease, severe aortic stenosis, uncontrolled arrhythmias, decompensated heart failure, acute myocarditis, severe peripheral arterial disease, cerebrovascular accident, thromboembolic disease, aortic aneurysm, clinically significant renal or hepatic failure, severe chronic obstructive pulmonary disease (COPD), clinically significant acute infections, severe psychiatric illness, uncontrolled metabolic diseases, musculoskeletal pathologies, or osteoporosis; (e) uncontrolled blood pressure (systolic blood pressure > 180 mmHg and diastolic blood pressure > 110 mmHg); (f) other pathologies contraindicating physical exercise, identified through the mandatory medical examination that all participants underwent; (g) participants not attending both of the assessments; and (h) participants of the TG who do not attend at least 75% of the sessions (Figure 1).

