### 2.5. Randomization and Blinding

Randomization was performed electronically using Microsoft Excel 2016 before the start of the program and pre/tests. An investigator not involved in participant recruitment conducted the randomization process following a randomization sequence (1:1). In addition, the examiners in charge of carrying out the evaluations will be blinded, and the participants will be instructed not to disclose the group to which they have been assigned to when the assessments are carried out.

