### 2.9. Statistical Analysis

The qualitative data from sociodemographic questionnaires will be summarized using frequencies, while the rest of the quantitative variables will be described using the mean and SD for both the TG and CG across different assessment time points. To ensure robust statistical evaluation, Type I (alpha) error control will be prioritized, with the Bonferroni correction applied to set the threshold for statistical significance at *p* = 0.05. Group comparisons will adhere to the intention-to-treat principle, incorporating necessary adjustments for adherence to the exercise program. Missing data will be handled using multiple imputation based on fully conditional specification (FCS), performed in SPSS 25.0 using the Multiple Imputation module.

To assess baseline characteristic differences between groups, the Student’s *t*-test will be used for parametric numerical variables, the Mann–Whitney U test for non-parametric variables, and the chi-square (χ^2^) test for categorical binary variables. Changes within and between the TG and CG from baseline to follow-up assessments will be analyzed using the appropriate tests. For variables with a normal distribution, a repeated-measures analysis of variance (ANOVA) will be applied. Post hoc comparisons will utilize *t*-tests with Sidak corrections to control Type I errors. For non-parametric variables, the Friedman test will be followed by the Wilcoxon test, with the Bonferroni correction applied for multiple comparisons. Sensitivity analyses will be conducted to assess the robustness of the main results under varying assumptions, including analyses with and without imputed datasets and potential alternative modeling strategies.

All statistical analyses will be conducted using SPSS version 25.0. A *p*-value of <0.05 will indicate statistical significance, with adjustments made for multiple comparisons as described above.

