### 2.10. Feasibility and Acceptability Assessment

Feasibility will be assessed using indicators such as recruitment rate, session attendance, retention rate, and adherence to the intervention protocol. Acceptability will be evaluated through a brief post-intervention questionnaire consisting of open-ended questions addressing participants’ satisfaction, perceived usefulness, and overall experience with the program.

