## Figures and Tables

**Figure 1 healthcare-13-01110-f001:**
[figure not shown]
Consolidated Standards of Reporting Trials flow diagram showing the flow of participants through each stage of the study. NOTE: The follow-up accounts for potential participant exclusion based on expected attrition observed in previous studies.

**Table 1 healthcare-13-01110-t001:** SPIRIT schedule of enrolment, interventions, and assessments.

Study Period	Enrolment	Pre-Intervention (Pre-Test)	Familiarization (2 Weeks)	Intervention (Weeks 1–18)	Post-Intervention (Post-Test)	3-Month Follow-Up (Re-Test 1)	6-Month Follow-Up (Re-Test 2)
Informed Consent	X						
Eligibility Screening	X						
Randomization	X						
Baseline Assessments		X					
Multidomain Intervention			X	X			
Outcome Assessments					X	X	X

**Table 2 healthcare-13-01110-t002:** Distribution of content between the weekly sessions.

Session Part	Content	Details	Monitoring	Cognitive Integration
Warm-up (10 min)	- Activation exercises - Joint mobility	Playful tasks and movement prep activities; progressive cardiorespiratory stimulus.	RPE (Borg), trainer supervision	Sensorimotor activities, coordination-based games
Main (40 min)	First weekly session Local muscle endurance (1) Balance and coordination	Circuit of 8 exercises (6 strength, 2 balance/coordination). 3–4 sets of 10–12 reps. 20–30 s rest between exercises. Equipment: dumbbells, bands, TRX.	OMNI-RES RPE (6–7/10), trainer diary	Dual tasks (e.g., movement + verbal/cognitive tasks)
	Second weekly session Power training + local muscle endurance (2) Cardiorespiratory	Power block: 3 exercises, 2 sets of 6–8 reps. Load moved as fast as possible. Local muscle endurance block: 3 exercises, 3 sets of 10–12 reps. Cardio: 2 × 4 min intervals, moderate to vigorous using the talk test.	OMNI-RES RPE, Borg scale, trainer diary	Dual tasks, attention/memory components
Cool-down (10 min)	- Flexibility - Relaxation - Emotional intelligence tasks	Static stretching (8 exercises, 10–30 s), body–mind exercises (Tai Chi, breathing), emotional intelligence games (collaboration, expression of feelings).	Trainer checklist	Breathing visualization, reflective and emotional tasks
Autonomous training	Brisk walking (2×/week)	30+ min per session, moderate intensity. Monitored via self-reported training diaries and talk test.	Training diary (duration, distance, RPE)	—

**Table 3 healthcare-13-01110-t003:** Description of outcome measures.

	Dimension	Test	Description

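### Exclusion criteria (g) and (h) act after randomisation, (h) in the training arm only, and contradict the intention-to-treat analysis promised in section 2.9

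*Protocol article*

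**What the plan says.** Timing. Section 2.4 of the protocol article states that "participant recruitment and randomization have already been completed", although baseline assessment and the intervention have not begun. Section 2.5 agrees: "Randomization was performed electronically using Microsoft Excel 2016 before the start of the program and pre/tests".

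Exclusions. The list in section 2.4 ends with "g) participants not attending both of the assessments; and (h) participants of the TG who do not attend at least 75% of the sessions". Criterion (g) can apply in either arm. Criterion (h) names the training group (TG) only.

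Analysis. Section 2.9 states: "Group comparisons will adhere to the intention-to-treat principle, incorporating necessary adjustments for adherence to the exercise program". It continues: "Missing data will be handled using multiple imputation based on fully conditional specification (FCS"), carried out in SPSS. The planned sensitivity analyses compare results with and without imputed data and mention alternative models. No per-protocol or completer set is named.

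Flow. The note to Figure 1 reads: "The follow-up accounts for potential participant exclusion based on expected attrition observed in previous studies".

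Feasibility. Section 2.10 lists as indicators "recruitment rate, session attendance, retention rate, and adherence to the intervention protocol" and does not state a denominator.

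**The concern.** An exclusion criterion normally decides who enters a trial. These two depend on behaviour that is seen only after allocation, so they decide who leaves. Criterion (h) makes the problem worse because it works on one side. A participant who would attend poorly is removed if allocated to training and kept if allocated to control, so the arms are no longer comparable by design. If people who attend more also tend to do better for other reasons, such as health or motivation, the training arm looks better even when the programme does nothing.

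The qualification inside the intention-to-treat sentence adds to this. Adherence is a post-randomisation quantity, and session attendance exists only in the TG. A main comparison adjusted for it in some unstated way need not estimate the effect of allocation.

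At stake is who is counted in every between-group comparison in the trial.

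**Working it through.** **Step 1: can (g) or (h) be judged before allocation?** Randomisation preceded the pre-tests and the programme (sections 2.4 and 2.5). Criterion (g) depends on attendance at assessments, all of which come after randomisation, including the pre-test. Criterion (h) depends on attendance at training sessions. So neither can be judged beforehand.

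**Step 2: the threshold in (h).** Section 2.6 gives 18 weeks at two supervised sessions per week: 18 × 2 = 36. Then 0.75 × 36 = 27, so a TG participant who attends 26 or fewer is excluded. The control group has no sessions (section 2.6), so no equivalent rule is possible there.

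**Step 3: the two sections side by side.**
- Section 2.9: analyse as randomised and impute what is missing.
- Section 2.4: remove those with missing assessments, and TG participants with low attendance.
- Nothing confines (g) and (h) to a secondary set. The sensitivity analysis with and without imputation would not bring removed participants back.

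These instructions are incompatible.

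**Step 4: how large could the selection effect be?** The plan gives no figure on this, so there is none to reproduce. From the documents I use 26 per arm (section 2.3). The following are assumed, because the documents do not give them: no true effect, a share q of the TG removed as the lowest attenders, and a correlation r between attendance propensity and outcome, with both normally distributed. Other dropout is ignored.

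With z the q-quantile of the standard normal and φ its density, let m = φ(z)/(1 − q). Then:
- spurious difference b = r × m, in SD units;
- variance among retained TG v = 1 − r² × m × (m − z);
- standard error = √[v/(26(1 − q)) + 1/26];
- two-sided type I error = 1 − Φ(1.96 − b/SE) + Φ(−1.96 − b/SE).

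Worked case, q = 0.25 and r = 0.5:
- z = −0.674, φ(z) = 0.318, m = 0.318/0.75 = 0.424.
- b = 0.5 × 0.424 = 0.212 SD.
- v = 1 − 0.25 × 0.424 × 1.098 = 0.884.
- SE = √(0.884/19.5 + 1/26) = 0.289, so b/SE = 0.73.
- Type I error ≈ 0.113.

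| q removed | r | b (SD) | Type I error |
|---|---|---|---|
| 10% | 0.1 | 0.02 | 5.1% |
| 15% | 0.3 | 0.08 | 5.9% |
| 25% | 0.3 | 0.13 | 7.1% |
| 25% | 0.5 | 0.21 | 11.3% |

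Simulations of the last row gave 10.2% and 10.4%, and one put the bias at 0.19 SD, so about 0.2 SD and 10% is a fair summary of the upper end shown. The lower end is practically nil.

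**The case against.** The strongest reply is that section 2.9 is the only place that states an analysis principle, and it says intention-to-treat with imputation. Section 2.4 is about recruitment, and its last two items may be loosely placed. That is fair as far as it goes: the article does not show that the exclusions would prevail, and a reader should not infer that the trial will certainly not be analysed by intention-to-treat. The contradiction stands all the same. The note to Figure 1, which expects exclusions at follow-up, gives the literal reading some support.

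Four stronger readings are tempting, and the documents do not support them.

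- *Imputation would have little left to do.* Four assessments are planned, so "g) participants not attending both of the assessments" is ambiguous. It most naturally means the pre-test and post-test, since section 2.8 adds the two re-tests separately. Missing re-tests and item-level gaps would then still need imputing.
- *Attendance will be a covariate, so the group effect becomes an extrapolation to zero attendance.* Section 2.9 names no model. The phrase could also cover a complier-average analysis. What can be said is that it is undefined and attached to the wrong sentence.
- *The feasibility aim is defeated because retention and attendance are high by construction.* That would follow only if the indicators were computed among those retained. Section 2.10 does not say so, and attendance is logged at every session, so rates over all randomised can still be computed.
- *Power falls from 75% to 68%.* This needs a further 25% of the TG lost on top of the 15% dropout allowance (16.5 v 22 analysed), and an effect of d = 0.81 back-solved on a two-sided test. Section 2.3 gives neither an effect size nor sidedness, and the note to Figure 1 suggests that exclusions may already be counted. With only (h) losses from 26 per arm (19.5 v 26), power at that effect is 75.6%.

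The trial is also described as preliminary, with results to be read cautiously. Section 2.3 ties that caution to the small sample and type II error. It does not deal with selection.

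**Conclusion.** The point holds as an internal contradiction that must be resolved. Section 2.4 removes randomised participants on post-allocation behaviour, one criterion acting on the training arm alone, while section 2.9 promises to keep them. The adherence wording leaves the main comparison further undefined.

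That much follows from the text alone. The size of any bias does not. It depends on how many TG participants fall below 27 sessions and how strongly attendance relates to outcome, and the documents give neither. Within the assumed range it goes from negligible to a fifth of an SD with type I error roughly doubled. The direction favours the programme if better attenders would have done better anyway.

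**What to change.** 1. Delete (g) and (h) from the exclusion criteria in section 2.4.
2. In section 2.9, define the main analysis set as all randomised participants in their allocated arm, whatever their attendance, with missing visits handled by the stated multiple imputation.
3. Remove the adherence adjustment from the intention-to-treat sentence.
4. Report participants with at least 75% attendance only in a labelled supplementary analysis, either per-protocol or, preferably, a complier-average estimate.
5. State in section 2.10 that the feasibility indicators take all randomised participants as their denominator.

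By the article's account neither baseline assessment nor the intervention has begun, so the analysis set can still be fixed without knowledge of outcomes. The cost is wording in sections 2.4 and 2.9, plus one clarifying sentence in 2.10. It needs no extra participants or visits. The effect estimate may come out smaller than one restricted to attenders.

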### 2.5. Randomization and Blinding

Randomization was performed electronically using Microsoft Excel 2016 before the start of the program and pre/tests. An investigator not involved in participant recruitment conducted the randomization process following a randomization sequence (1:1). In addition, the examiners in charge of carrying out the evaluations will be blinded, and the participants will be instructed not to disclose the group to which they have been assigned to when the assessments are carried out.

### 2.6. Intervention

The TG will follow an outdoor multidomain training program in groups of no more than six participants. All sessions will take place in an open-air facility, equipped with sports equipment such as dumbbells, kettlebells, plyometric boxes, sandbags, resistance bands, and other functional training materials. Although cognitive training is a structured component of the intervention, activities related to emotional intelligence will be incorporated separately through playful, interactive, and socially engaging tasks. These will be intended to support emotional and relational well-being and are evaluated as an independent exploratory outcome.

The outdoor multidomain training program will include resistance training, cardiorespiratory, balance, coordination, flexibility, relaxation, playful and relational tasks related to emotional intelligence, and cognitive training. The program will be based on the HEALTHY-AGE multidomain intervention [45], and it is designed for middle-aged and older people, with the weekly distribution of session content detailed in Table 2. The program will have a duration of 18 weeks of training, with a frequency of two days per week and a duration of 60 min per session conducted face-to-face. The training sessions will be divided into three parts and will include the following components: (1) warm-up (10 min): activation exercises and joint mobility exercises; (2) main part (40 min): resistance training, cardiorespiratory training, and balance and coordination; and (3) cool-down (10 min): flexibility, relaxation, and playful and relational tasks related to emotional intelligence. Cognitive tasks will be integrated in a cross-cutting manner in all parts of the session.

The cognitive component will progressively increase in complexity across the 18-week period, beginning with basic sensorimotor and attention tasks, and gradually incorporating dual-task challenges, memory recall, and executive function elements. Trainers will be guided by a structured progression plan to ensure appropriate cognitive load and adaptation for each participant. Adherence will be monitored daily using electronic forms completed by the trainers. Attendance will be recorded for each session, along with an evaluation of each participant’s performance based on session objectives, exercise intensity, volume, and overall engagement.

In addition, to supervise multidomain training and based on the exercise recommendations [46,47], participants of the TG will be instructed to autonomously walk briskly (cardiorespiratory training) for two additional days per week, with each session lasting at least 30 min at moderate intensity, while using the talk test for perceived exertion [48]. Participants will receive training on how to use the talk test during the first week of the intervention. Additionally, participants from TG will be encouraged to use the mobile phone pedometer to keep track of the distance they cover. The intensity of the session will be monitored by the Borg Rating of Perceived Exertion Scale (target score: 6–7/10) [49]. Participants will have to keep a training diary indicating the days they complete this type of training, the time they walk, the distance covered, and the rating of perceived exertion at the end of the session, following the methodology of previous studies [45].

In every week, the same blocks of contents will be maintained for the first session of the week; and the same blocks of contents for the second session of the week. The training program was designed in accordance with the recommendations provided by the National Strength and Conditioning Association (NSCA; Fragala et al., 2019) and the American College of Sports Medicine (ACSM; Liguori, 2020), respecting the periodization to avoid reaching muscle failure and considering personalization and the nature of the effort [46,50,51].

The activation exercises will consist of different tasks and games that integrate joint mobility and some movements such as those from the main part, with a playful component while generating a progressive stimulus at the cardiorespiratory level to prepare for the session.

Resistance training will include multi-joint exercises targeting major muscle groups participating in the daily activities, including vertical and horizontal push and pull movements, hip-dominant and knee-dominant exercises, and the activation of the trunk musculature. Specific equipment such as dumbbells, barbells, kettlebells, suspension training, and resistance bands, will be used throughout the entire program [45]. The volume and intensity of the training will increase gradually on an individual basis based on ACSM and NSCA recommendations.

The resistance training in the first weekly session will consist of a circuit of local muscular endurance training (vertical organization) of 8 exercises, with 3–4 sets of 10–12 repetitions and a recovery of 20–30 between exercises and 1 between sets. As for the nature of the exercises, six of them will be strength exercises, while the other two will work on balance and coordination as the main objective. For balance and coordination work, gradual progression will be implemented by increasing and varying the base of support, support surface, type of stimulus, and information used for balance exercises. Examples will include progressing from bipodal support to a semi-tandem position, progressing from eyes open to eyes closed, and performing dynamic movements that involve the displacement of the center of gravity. Activities targeting the postural muscles such as walking on tiptoes, heels, or backwards will also be included. The intensity of the circuit will be measured by perceived exertion, aiming for an intensity of 6–7 out of 10 on the OMNI-RES Perceived Exertion Scale [49,52].

In the second session of each week, both the power training and local muscle endurance training will be included. The power block will always be carried out first and the local muscle endurance block second. For the power block, the following shall be performed: 3 exercises, with 2 sets of 6 to 8 repetitions and a recovery of 1’ between exercises and sets, following a horizontal organization. The external load will be such that a maximum of 1 or 2 repetitions in reserve (RIR) is reached, and the load will be moved as fast as possible. The intensity of this part of the session will be measured by perceived exertion, aiming for an intensity of 6–7 out of 10 on the OMNI-RES Perceived Exertion Scale [46,51].

As for the local muscle endurance training after the power work, a circuit (horizontal organization) of 3 strength exercises will be performed at a rate of 3 sets of 10 to 12 repetitions, with rests of 20 to 30’ between exercises and 1’ between sets. The intensity of this part of the session will be measured by perceived exertion, aiming for an intensity of 6–7 out of 10 on the OMNI-RES Perceived Exertion Scale [46,51].

The cardiorespiratory component of the intervention will involve two sets of four-minute bouts of continuous aerobic activity, with a 40-second rest between sets. The participants will be instructed to begin at a moderate intensity and gradually increase to a vigorous pace, guided by their ability to speak comfortably during exercise (i.e., the talk test) [48]. Exercise intensity will be further monitored using the Borg Rating of Perceived Exertion Scale, aiming for a perceived effort of 6–7 out of 10 [49].

Flexibility training will be based on passive static exercises in the cool-down period. Exercises will consist of eight stretching exercises of one or two sets of 10 to 30 s per each one, with 15 s of rest between sets and exercises. The relaxation block will consist of different breathing exercises, body–mind movements (Tai Chi, Pilates, etc.), which will integrate breathing. With respect to the emotional intelligence task, this block will consist of different games involving collaborative tasks, expression of feelings, etc.

Furthermore, cognitive training will be systematically integrated into each session through targeted, structured strategies consistent with the multidomain approach. Each session will include 2 to 4 cognitive-motor tasks, depending on duration and participant capacity, ensuring regular engagement without cognitive overload. These tasks will be standardized across sessions but adapted in complexity to match individual progression. As described in neuropsychological frameworks [22], such activities are structured to stimulate various cognitive processes while allowing for scalable difficulty. Strategies will include association tasks (e.g., linking specific movements to auditory or visual stimuli such as clapping when hearing a specific color name), memory recall and sequence reproduction (e.g., performing a series of steps in a set order and repeating them backward), and multisensory activities (e.g., touching textured objects while responding to verbal cues). Dual-task challenges—such as stepping in time while naming words starting with a given letter—will gradually increase in complexity to promote executive function. Additional components include body representation exercises (e.g., mirroring movements or identifying touched body parts with eyes closed), attention and observation games (e.g., responding only to specific shapes or colors in a movement sequence), verbal and numerical challenges (e.g., pairing movements with math operations), spatial-temporal tasks (e.g., navigating timed obstacle paths), problem-solving through movement (e.g., assembling patterns with body positioning), and guided relaxation with visualization to support mental recovery. These cognitively enriched physical tasks will aim to enhance participant engagement, promote adherence, and stimulate core cognitive domains such as memory, attention, and executive function—key targets of effective multidomain interventions [45,53].

The ACTIVA-Senior program was designed by a group of researchers from the University of Almeria, in collaboration with the Healthy Age—Active Aging, Exercise and Health Network of the “Consejo Superior de Deportes” (Spain), who have extensive experience in the design of similar interventions. The program will be delivered by five certified trainers with a BSc in Sport Science and an MSc in Physical Training.

To enhance replicability, the intervention will follow a clearly structured session format with predefined warm-up, main, and cool-down segments, which are consistently applied across the 18-week period. All sessions will be delivered by certified professionals with a BSc in Sport Science and an MSc in Physical Training, with standardized training prior to the intervention to ensure consistency. Intervention fidelity is expected to be monitored through trainer-completed session logs, including detailed records of attendance, content delivery, perceived exertion, and participant engagement. The progression of training volume and intensity will be guided by established criteria based on perceived exertion scales (OMNI-RES and Borg), with adaptations made individually to align with the participant’s capacity and safety guidelines.

Participants will be encouraged to incorporate the exercise program into their life routine after the intervention ends. Strategies will include providing participants with personalized exercise plans to continue at home, offering follow-up support through periodic check-ins, and promoting community or group-based exercise opportunities to foster social support and accountability. Additionally, resources and information on local fitness opportunities or programs will be provided to help participants stay active in the long term.

As for the participants in the CG, they will not be enrolled in any training program and will be instructed to continue with their regular level of physical activity, nutrition, and habits during the study. However, participants in the control group will undergo pre-test, post-test, re-test 1, and re-test 2 assessments and will complete the same questionnaires as the experimental group.

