### 2.3. Sample Size and Power Calculation

The sample size was calculated using RStudio 3.15.0 software (RStudio Inc., Boston, MA, USA) prior to the recruitment of participants. Assuming a study design with a 5% Type I error rate and 75% statistical power, the calculation was informed by effect sizes reported in similar multidomain interventions. These effect sizes were drawn from studies targeting physical, cognitive, and psycho-physiological outcomes in older adults [41,42,43]. A potential 15% dropout rate has been accounted for in the final estimate [44]. This yielded a total sample size of 52 participants (26 per group). While this sample size is considered sufficient to detect meaningful changes, the relatively small cohort may increase the risk of Type II errors. Therefore, upon completion of the trial, the results will have to be interpreted with caution and regarded as preliminary until validated by studies with larger samples.

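### The training arm is taught in small groups and the control arm is not, but the named tests treat everyone as independent; if outcomes correlate within groups, standard errors will be too small

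*Protocol article*

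**What the plan says.** All references are to the protocol article.

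- **Delivery in the TG (section 2.6).** "The TG will follow an outdoor multidomain training program in groups of no more than six participants". On staffing: "The program will be delivered by five certified trainers with a BSc in Sport Science and an MSc in Physical Training". The section does not say whether a participant stays in one training group for the 18 weeks, or how trainers are assigned to groups.
- **CG (section 2.6).** Controls are not enrolled in any training and keep their usual habits, so they have no training-group structure.
- **Randomization (section 2.5).** Allocation is 1:1, with no cluster or stratum mentioned.
- **Sample size (section 2.3).** The total is 52, or 26 per group. The only inflation named is for attrition: "A potential 15% dropout rate has been accounted for in the final estimate".
- **Analysis (section 2.9).** For normally distributed variables, "a repeated-measures analysis of variance (ANOVA) will be applied", followed by Sidak-corrected t-tests. Other variables get Friedman and then Wilcoxon tests. None has a training-group or trainer term. Sensitivity analyses include unspecified alternative models; clustering is not named. The same section makes control of type I error a priority.

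**The concern.** This is a partially nested design: individual randomization, with clustering created by delivery in one arm only. Members of a training group share sessions, companions and probably a trainer. The protocol treats shared experience as part of the treatment. Section 1 counts social engagement among the components and expects social interaction to strengthen the effect, and section 2.6 describes collaborative games. Emotional state, life satisfaction and motivation are among the outcomes, and it is plausible that these move together within a group.

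If they do, the TG mean is less precise than 26 independent people would make it, and the named tests do not see this. Intervals for the TG-CG difference would be too narrow and p-values too small, which works against the stated priority. The variance handed to the later trial would also be understated.

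**Working it through.** **1. The plan's own figure.** Inputs from section 2.3: "Assuming a study design with a 5% Type I error rate and 75% statistical power", 15% dropout, 52 in total. No effect size is given, only that "the calculation was informed by effect sizes reported in similar multidomain interventions", so 52 cannot be reproduced from the stated inputs. Assuming a two-sided comparison of two independent means:

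- n per arm = 2(1.960 + 0.674)² / d². With an assumed d = 0.80 this is 21.7, so 22; and 22 / 0.85 = 25.9, so 26 per arm and 52 in total.
- Back-solving from 22 evaluable per arm gives d = 0.79.

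So 52 is consistent with a calculation for independent participants that has no design effect, though this does not prove that it was the calculation used.

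**2. Number of training groups.** 26 / 6 = 4.3, so at least five groups, with mean size 26 / 5 = 5.2. For sizes 6, 5, 5, 5, 5 the effective size is (36 + 4 × 25) / 26 = 5.23.

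**3. Variance inflation, TG only.** The TG design effect is DE = 1 + (5.23 − 1) × ICC. The CG has DE = 1. With equal arms, the variance of the difference is multiplied by (1 + DE) / 2. The ICCs are assumptions. For a group-by-time effect, the relevant ICC is that of the change being tested.

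**4. Simulation.** An ordinary t-test, 26 TG participants in five groups against 26 independent controls, with no true effect and 100,000 runs per setting:

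| Assumed ICC | TG design effect | Variance ratio | √ of ratio | True SE / naive SE (simulated) | Actual type I error |
|---|---|---|---|---|---|
| 0 | 1.00 | 1.00 | 1.00 | 1.005 | 4.95% |
| 0.01 | 1.042 | 1.021 | 1.011 | 1.014 | 5.2% |
| 0.05 | 1.212 | 1.106 | 1.052 | 1.059 | 6.2% |
| 0.10 | 1.423 | 1.212 | 1.101 | 1.107 | 7.5% |
| 0.20 | 1.846 | 1.423 | 1.193 | 1.210 | 10.1% |

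The simulated ratio slightly exceeds the formula because the naive sample variance in the TG also misses part of the between-group component.

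**5. Within-TG changes.** Section 2.9 also tests changes within each arm. There the full TG design effect applies: √1.212 = 1.10 at ICC 0.05 and √1.423 = 1.19 at ICC 0.10.

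**6. Power.** This uses 22 evaluable per arm, d = 0.79, a normal approximation and the correct standard error. At ICC 0.10, power falls from 75% to 68% if the 22 TG participants sit in five groups, or to 66% if in four.

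**7. Does the remedy work with so few groups?** In a simulation of the layout in step 4, with a between-group variance term and Satterthwaite degrees of freedom, type I error was about 3.5% to 5.5%. The group variance was estimated at or below zero in about 35% to 45% of runs at true ICCs of 0.10 to 0.05.

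**The case against.** - **The bias is conditional.** It needs a positive ICC and reasonably stable groups or trainers, and the article states neither. Only a maximum group size is given, and rescheduling for weather (section 2.1) could mix groups. If people rotate, simple nesting does not describe the data. This stands, and it is why the point is worded with an if.
- **Parts of the design limit clustering.** Trainers are trained to a common standard, two weekly walking sessions are done alone, and the group games share a 10-minute cool-down with other content. Many outcomes are physical measurements such as handgrip, bioimpedance and blood pressure. A reader might count individually adapted progression as a source of within-group correlation, but the protocol describes tailoring to the person, which is not a group-level exposure. A reader might also apply ICC 0.20 to every outcome; nothing in the article supports that.
- **The effect can be small.** At ICC 0.01 the type I error is 5.2%, and the trial calls itself preliminary. True, but it becomes material from about ICC 0.05.
- **Five groups are few.** The group variance will often be estimated at zero. This limits what can be learned about the ICC, but step 7 shows that the test remains usable.
- **A fuller plan may cover it.** A random effect is the kind of detail such a plan can hold, and section 2.9 leaves room for alternative models. That answers the point only in part, because the article commits to named tests that assume independence and never mentions clustering.

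**Conclusion.** The point holds in conditional form. The partially nested structure and the independence-based tests are both on the page. If outcomes correlate within stable training groups, standard errors for TG-CG differences are too small: the true value is about 1% / 6% / 11% / 21% above the naive one at assumed ICCs of 0.01 / 0.05 / 0.10 / 0.20, with type I error of about 5.2% / 6.2% / 7.5% / 10%. At ICC 0 nothing is lost. These figures rest on five groups of near-equal size, fixed membership, normal outcomes and ICCs that the documents do not supply.

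A reader might infer that the standard errors are definitely too small, or that the sample of 52 is thereby shown to be wrong. The documents support neither: no ICC is given, fixed membership is not stated, and the effect size behind 52 is not reported. The weight is moderate, and the point is worth acting on because the correction is inexpensive and section 2.4 says that baseline assessment and training have not begun.

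**What to change.** 1. Record training group and trainer for each TG participant at each session, in the forms and logs that trainers already complete. State in section 2.6 whether membership is fixed and how trainers are assigned.
2. In section 2.9, add a partially nested mixed model: a random training-group intercept in the TG only, controls as singletons, and Satterthwaite or Kenward-Roger degrees of freedom. Make it at least a named sensitivity analysis. If the group variance is estimated at zero, report that and the model fitted.
3. Show the main TG-CG results over a range of assumed ICCs, for example 0 to 0.20, since one estimate from about five groups will not settle the matter.
4. Report any estimated ICC with its confidence interval, and say that it should not be used alone to plan the later trial.

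**Cost.** One or two recorded fields and one random term; randomization is unaffected. Intervals become somewhat wider, and the group variance will be imprecise and often estimated at zero.
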